### 2.18. Data Dissemination

The information collected from patients, after statistical analysis, would be given to the allocated principal investigator in the field staff, who will serve as independent witnesses. The information from the research meetings in the study will become the property of the trial ethics committee, and they may request to discuss the individual information of the LRTIs patients in order to evaluate their therapy improvement. Authorship of the journal publication will be decided according to the guidelines described by the International Committee of Medical Journal Editors (ICMJE).

### 2.19. Adverse Event Monitoring

All the events related to adverse drug events (ADEs) occurring as a result of anti-infective therapy will be recorded by field staff. The ADRs will be observed and within 48 h, it will be decided whether the event occurred due to the antibiotics or other medicines. Trial staff will determine the appropriate action if necessary. The principal investigator will be in contact with the trial participants and ethical approval bodies.

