## Abstract

Globally, lower respiratory infections (LRTIs) are one of the most common infectious diseases whichaffect majority of the population and as a result of inappropriate antibiotics practices lead to antibiotic resistance (AR). An individual randomized control trial will be conducted in the post-conflict areas of Swat, Pakistan, through a random sampling method. Patients aged > 18 years will be recruited from five community pharmacies and assigned to equally sized groups to receive either pharmacist-led education interventions or usual care with no intervention. A total of 400 (control = 200, study = 200) patients will be included, with prescriptions comprised of antibiotics for LRTIs. The outcomes measured in both groups will be a combination of treatment cure rate and adherence, which will be assessed using the Morisky Medication Adherence Scale and pill count. The trial comprises pharmacist-led educational interventions to improve treatment outcomes for patients with LRTIs. This study might establish the groundwork for pharmaceutical care of LRTIs patients with antibacterial therapy and the future delivery of a care strategy for the improvement of LRTIs treatment outcomes in post-conflict, remote areas of the third world and LMICs.

**Trial registration**: Chinese Clinical Trials Registry, identifier: ChiCTR2000040453, registered on 28 November 2020.

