## 1. Introduction

Lower respiratory tract infections (LRTIs) are a type of acute sickness that lasts for 21 days or less and is characterized by the presence of at least one other lower respiratory tract symptom, in addition to the main symptom of cough (dyspnea, sputum, wheeze, or chest discomfort, and pain), with no other suitable explanation (e.g., sinusitis or asthma) [1]. Globally, LRTIs are one of the leading infectious diseases, the fifth overall cause of death, and the second most common cause of disability adjusted life years (DALYs), despite their being mainly preventable causes of mortality and morbidity [2]. Over the last ten years, the epidemiology of LRTIs has changed, with a rise in patients over the age of 70 [2]. LRTIs have no specific definitions besides the epidemiological perspective. LRTIs comprise bronchitis, acute exacerbations in chronic obstructive pulmonary disease (AECOPD), chronic obstructive pulmonary disease (COPD), pneumonia, community-acquired pneumonia (CAP), bronchiolitis, and influenza [2,3,4]. The LRTIs (2015) global burden of disease study noted that LRTIs were assessed to have caused 103.0 million DALYs and 2.74 million deaths [2]. However, pneumococcal pneumonia was found to be a cause of 55.4% of deaths in all age groups [2]. Worldwide studies from different regions, including North America [5], Latin America [6], Europe [7], and the Asia Pacific region [8], indicate the noteworthy clinical and economic load of the CAP disease. Antibiotic resistance was reported among CAP, with common pathogens, predominantly Streptococcus pneumoniae [5,8]. An African study reported that the pneumococcus remained susceptible to ampicillin/amoxicillin, which can still be used to treat the illness. The 1918 influenza pandemic killed over 50 million people, and while most influenza virus infections are self-limiting, there is still a significant number of severe infections that result in deaths, as influenza plays a considerably larger role in the etiology of CAP and AECOPD [9,10]. Moreover, patients with severe COPD and prone to acute exacerbations have more experience with antibiotics, and resistance may develop [11].

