Nonetheless, antibiotics are still used for the treatment of LRTIs, resulting in the development of antimicrobial resistance [12,13]. Antimicrobials were originally regarded as lifesavers, with the best cure being antibiotics. However, incorrect antibiotic usage in the treatment of respiratory diseases might result in the emergence of resistance [14,15,16]. Antibiotics were misused in clinics because numerous isolates revealed high levels of antibiotic resistance; consequently, efficient antibiotic resistance surveillance is urgently needed to limit antibiotic abuse in China and Indonesia [17,18]. Treatment failure was more common in patients with RTIs in Pakistan because treatment outcomes are linked to antibiotic resistance [19].

Educational interventions could increase appropriate antibiotic prescription, dispensing, and/or use, which are commonly employed multimodal interventions [20,21,22]. Educational interventions at the community level reported a lower rate of antibiotic prescription, and enhanced knowledge of and attitudes towards antibiotic misuse [23]. Therefore, there has been no coverage of the topic, including educational interventions on patients recruited at community pharmacies, to improve adherence to antibiotic therapy in Pakistan. Hence, one of the barriers to care is the physical distance of rural communities from urban healthcare facilities. One of our baseline studies reported that the education of rural people is key to reducing the misuse of antibiotics [24].

The post-conflict areas (Swat) of Pakistan have witnessed extensive militancy since 2007. This has continued for many years, as the majority of the population of rural areas were displaced and migrated to the safest areas of the country [25]. During 2009, the people of Swat were asked to return after the area was cleared; however, the unremitting military presence and intermittent conflicts between security agencies and militants remain a social restiveness [26]. In the post-conflict areas of Swat, misuse of antibiotics occurs at a high frequency [24]. To address this gap, brief educational interventions will be delivered to the patients with LRTIs.

Therefore, this study aims to determine the adherence to prescribed antibiotics through educational interventions in post-conflict rural areas of Pakistan.

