## 2. Materials and Methods

### 2.1. Objectives and Hypothesis

The main objective of the current trial is to test the adherence to LRTI treatment in the local/rural villages of Swat, Pakistan. The secondary objective is to assess the improvements and the success rate of the therapy. First, the quantitative part will be completed; then, a qualitative interview will be conducted.

The primary hypothesis is; the intervention group will gain knowledge of, and adhere to, the prescribed therapy for LRTIs at a higher rate than the control group at 2 and 7 weeks. The secondary hypothesis is as follows.

Post-assessment will be conducted in the second week and endpoint evaluation at the end of seventh week; participants who received the intervention are expected to report positive changes in terms of their adherence to the medication and a reduction in antibiotic storage. After the seventh week, those in the intervention group are more likely to stick to their prescribed medication. Following the quantitative phase of the research, a qualitative assessment will be conducted to determine its acceptability.

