**INTERVENTIONS:**									
leaflets									
Booklets									
WHO awareness									
Usual Care									
**ASSESSMENT:**									**Outcomes analysis**
Baseline variables	x	x	x	x	x	x	x	x	
Therapy success rate	x	x	x	x	x	x	x	x	
Primary Outcomes									
Overall Adherence Secondary Outcomes	x	x	x	x	x	x	x	x	

**Table 3 antibiotics-10-01147-t003:** Overall trial blinding strategies.

Stakeholders	Allocation	Pharmacist-Led Interventions	Community Pharmacists	Outcome Assessment	Data Analysis
Trial Observer (PI)	a	a	a	a	a
Trial Participants	n/a	n/a	n/a	n/a	n/a
Duty Pharmacists	n/a	a	a	n/a	n/a
Data accumulators	n/a	n/a	n/a	n/a	n/a
Data analysts	n/a	n/a	n/a	n/a	a

a: aware; n/a: not aware. PI: principal investigator.

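### Section 2.19 selects adverse events by a cause it has yet to decide, and offers no non-drug cause, so infection-related events have no stated route into the safety data

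*Protocol article*

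**What the plan says.** The safety text is one short section, 2.19. On scope it says "All the events related to adverse drug events (ADEs) occurring as a result of anti-infective therapy will be recorded by field staff". On cause it says that, within 48 h, "it will be decided whether the event occurred due to the antibiotics or other medicines". On what follows, trial staff decide whether action is needed, and "The principal investigator will be in contact with the trial participants and ethical approval bodies". The section mentions neither admission nor death, and names no cause other than a drug.

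Clinical course appears elsewhere as an outcome. The abstract states that "The outcomes measured in both groups will be a combination of treatment cure rate and adherence". Section 2.1 adds that "The secondary objective is to assess the improvements and the success rate of the therapy". Table 2 has a row labelled "Therapy success rate", marked at T1 and at W1 to W7. Sections 2.11 and 2.13 have treatment outcomes checked around the end of the first week, by telephone if need be. Section 2.5.2, however, equates therapy success at the first call with the rate of adherence, and section 2.14.2 lists only adherence (MMAS-8 and pill count) as the secondary outcome.

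**The concern.** Safety recording normally runs in a fixed order: write the event down, then judge its cause. Section 2.19 puts a causal judgement into the definition of what is written down and then schedules the same judgement for later. Staff who follow the first sentence must form a view on cause before they record. An event that they do not record cannot be re-attributed at 48 h or recovered at analysis.

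The closed choice of causes adds to this. The introduction ranks lower respiratory infection as "the fifth overall cause of death" worldwide and says of the local setting that "Treatment failure was more common in patients with RTIs in Pakistan because treatment outcomes are linked to antibiotic resistance". Those statements are background, not estimates of risk in this trial, but they show that the authors regard the infection as a source of serious harm. Table 1 admits suspected and definite community-acquired pneumonia and acute exacerbations of COPD. The intervention aims to change how patients take their antibiotics, so the course of the infection is one way in which it could help or harm. The stated safety rule has no place for that kind of event.

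**Working it through.** No arithmetic applies. Apart from the 48 h window, section 2.19 contains no figure. The check is to apply each sentence to the kinds of event that may arise.

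| Event | Qualifies under the scope sentence? | Has a category under the causality sentence? |
|---|---|---|
| Reaction to the antibiotic | Yes | Yes |
| Reaction to another medicine | No | Yes |
| Worsening of the infection, with or without admission or death | No | No |
| Any other non-drug event | No | No |

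**Row 2 shows the conflict.** If the scope sentence governs, every recorded event is already due to the antibiotic and nothing remains to be decided. If the causality sentence governs, events due to other medicines must have been recorded, and the scope sentence is too narrow. Both cannot hold as worded.

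**Row 3 shows the gap.** It remains whichever sentence governs, because both are confined to drugs. If staff did record such an event, they would have to assign it to a drug or leave the cause blank. The first would overstate drug-attributed events; the second would leave the event outside the stated scheme.

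**Do the outcome measures cover row 3?**

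- The abstract and section 2.1 name cure, improvement and success of therapy, but neither defines them.
- The Table 2 row is marked at every time point, including T1, and does not say what is measured.
- Section 2.5.2 makes therapy success at the first call a measure of adherence. A patient who takes every dose and still worsens could count as a success on that definition.
- Section 2.14.2 specifies adherence alone.

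The article therefore shows an intention to follow clinical course, but no definition under which deterioration, admission or death would be identified, and none of it is presented as safety reporting.

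**Is there an occasion to record?** Section 2.5.2 follows patients to week 7 by telephone, and section 2.6 gives both arms routine calls. Wider recording can use these contacts and needs no new visit.

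**The case against.** The strongest reply is that this is loose English in a condensed article. The text does not say that other events are excluded, and the causality sentence makes sense only if staff record suspected drug events first and attribute them later. Definitions of serious events, reporting procedures and full causality lists are commonly left to the full protocol and its forms, which are not shown. Concentrating on antibiotic reactions is also defensible for an educational intervention, since better adherence mainly raises drug exposure.

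Much of this stands. Silence on serious-event procedures is no finding here, and the charitable reading may well be what was meant. But the article is not merely brief: it states a scope and a choice of causes, and the two disagree. Even the charitable reading covers suspected drug events alone, so row 3 of the table stays empty.

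The reply also rules out several stronger inferences that a reader might draw:

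- **That infection-related events are never captured.** Section 2.19 does not exclude them, and the cure and therapy success measures may pick up some failures to improve.
- **That the recording staff know the arm, so that under-recording differs by arm.** Table 3 lists data accumulators as not aware at every stage, and field staff are not matched to any row of it. Pharmacists deliver the counselling, so awareness is possible, but the document does not settle the matter.
- **That deaths and admissions would be counted as dropouts.** No section says how they are classified. The 20% attrition in section 2.7 is a sample-size allowance.
- **That some number of serious events would be lost.** The article gives no rate for this population, which consists of people who bring prescriptions to community pharmacies and have no extra comorbidities (section 2.8).

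**Conclusion.** The point holds as a defect in the stated rule. Section 2.19 selects events by a cause that it then leaves open, and its choice of causes contains no non-drug category. As written, it provides no route for infection-related deterioration, admission or death to be recorded as safety data, and the outcome measures elsewhere do not reliably make up for this.

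The size cannot be expressed as a number, because the document contains no event rate. The consequence is limited to safety reporting: no primary or secondary estimate depends on section 2.19. The conclusion rests on the wording of that section and on the article being what staff would follow. If the full protocol already has events recorded regardless of cause, the article's wording should be brought into line with it.

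**What to change.** Reword section 2.19 in three respects.

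1. **Recording.** Field staff record every untoward medical event, hospital admission and death, in both arms and regardless of suspected cause, at the contacts already planned.
2. **Attribution.** Cause is assigned only after the event has been recorded. To the two drug categories, add one for the underlying infection or its progression and one for other causes.
3. **Reporting.** All recorded events, admissions and deaths are reported by arm, in total and by assigned cause.

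The change needs new wording and a few extra lines on the data collection form. The downside is slightly more recording work at each contact; no new staff or visits are needed. How patients are treated is not affected.

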## 3. Discussion

The authors are not aware of a theory that can be utilized to support the development of interventions aiming to enhance adherence to prescribed antibiotics and discourage the household storage of antibiotics in Pakistan. Hence, the overall goal of this study is to assess whether an intervention by authors with educational leaflets will enhance adherence and reduce the storage of unused antibiotics in households taking antibiotics. There is a possible association between adherence to prescribed antibiotic use and general beliefs about antibiotic storage. This study is based upon the existence of evidence that people use antibiotics in the wrong way. This is the most ignored area in the country at the community level. Additionally, the present study aims to contribute, on a humanitarian level, to the existing knowledge, along with the related factors regarding the inappropriate use of antibiotics.

Pakistan has a high rate of excessive use of medications compared to other low–middle-income countries (LMICs) with irrational prescribing, high amounts of injectables (antibiotics), costly drugs, inappropriate dispensing, and weak regulations for community pharmacies [42]. Policy targets are limited, and comprise a high rate of drug registration, poor enforcement of essential drug lists and management protocols, industry access to healthcare professionals, and private sector regulations [42]. These are the main issues from the higher to community levels, which lead to antibiotics users storing antibiotics for use without any consultation with a physician or regard to the storage conditions. These determinants lead to the inappropriate use of antibiotics and, ultimately, antibiotics resistance is a likely the result of this misuse. Hence, there is an utmost need to engage the community and all stakeholders, including the local people, to stop the irrational use of antibiotics [24,43,44,45,46,47,48].

In conclusion, once antimicrobial drugs were considered curative and lifesavers. At present, due to the global emergence of AMR, the value of these agents is under pressure. Many factors are leading to the storage of antibiotics at home, and this can raise rates of misuse, increase antibiotics’ resistance, increase wastage, and cause patients to fail to adhere to therapy.

## Figures and Tables

**Figure 1 antibiotics-10-01147-f001:**
[figure not shown]
Schematic flow diagram of the trial.

**Table 1 antibiotics-10-01147-t001:** Definition related to LRTIs.

Terms	Definition
AB (Acute Bronchitis)	A patient with no chronic lung disease, acute sickness, symptoms connected to or clinical evidence that accompanies cough, which may/may not be productive, with LRTI advised and no alternative explanation (i.e., asthma/sinusitis).
Suspected community-acquired pneumonia	Cough and fever for more than four days with at least one new symptom chest, or dyspnea, and no other obvious causes.
Definite community-acquired pneumonia	Same as the above, according to the outcomes of lung studies of chest radiographs, shadowing in the elderly, followed by acute clinical (unspecified) disease for no apparent reason.
Acute exacerbation of COPD	An occurrence in the course of the sickness characterized by the patient’s receding symptoms of cough, dyspnea, and sputum, as well as their day-to-day inconsistency, sufficient to allow for a change in treatment.
Acute exacerbation of bronchiectasis	A decline in the patient’s baseline dyspnea, sputum, and regular cough beyond inconsistency, sufficient to necessitate a change in care in a patient with bronchiectasis.
Influenza	Acute illness characterized by increased cough, body aches, headache, and sore throat, often accompanied by a fever.

**Table 2 antibiotics-10-01147-t002:** Schedule of enrolment, interventions, and assessment; standard protocols items: recommendations for intervention trials (SPIRIT).

	STUDY PERIOD								
	Enrollment	Allocation	Post Allocation						Close-Out Time
**TIME POINT**	**T1**	**W1**	**W2**	**W3**	**W4**	**W5**	**W6**	**W7**	
ENROLLMENT:									
Eligibility									
Consent									
Baseline Data									
Allocations									
**INTERVENTIONS:**									
leaflets									
Booklets									
WHO awareness									
Usual Care									
**ASSESSMENT:**									**Outcomes analysis**
Baseline variables	x	x	x	x	x	x	x	x	
Therapy success rate	x	x	x	x	x	x	x	x	
Primary Outcomes									
Overall Adherence Secondary Outcomes	x	x	x	x	x	x	x	x	

**Table 3 antibiotics-10-01147-t003:** Overall trial blinding strategies.

Stakeholders	Allocation	Pharmacist-Led Interventions	Community Pharmacists	Outcome Assessment	Data Analysis
Trial Observer (PI)	a	a	a	a	a
Trial Participants	n/a	n/a	n/a	n/a	n/a
Duty Pharmacists	n/a	a	a	n/a	n/a
Data accumulators	n/a	n/a	n/a	n/a	n/a
Data analysts	n/a	n/a	n/a	n/a	a

a: aware; n/a: not aware. PI: principal investigator.

## Data Availability

Study investigators and all the health care providers can access the patient data.

## Abbreviations

LRTIs: Lower respiratory tract infections, BMQ: belief about medications questionnaires, PAS-QA: public awareness surveys questionnaire, MMAS-8: Morisky Medication Adherence Scale, RCT: Randomized Controlled Trial, COPD: chronic obstructive pulmonary disease AECOPD: acute exacerbations in chronic obstructive pulmonary disease, CAP: community-acquired pneumonia, LMICs: low–middle-income countries, AMR: antimicrobial resistance, AMS: Antimicrobial stewardship.
